Azathioprine is an immuno suppressant that has been used in other immune mediated diseases both as monotherapy and in combination with prednisolone as a steroid-sparing agent.20 It is metabolized to mercaptopurine by the enzyme thiopurine methyltransferase. It is widely used for organ transplant recipients and to treat a number of autoimmune conditions, usually when corticosteroid therapy alone provides inadequate control. 21

A recent trial conducted in Nepal using a three-month course of Azathioprine along with Prednisolone showed that addition of Azathioprine reduces the corticosteroid requirement for treatment of type 1 reactions. Although the clinical outcomes were similar for patients treated with either the prednisolone/azathioprine combination or prednisolone alone, the overall dose of prednisolone was less in those on the combined regimen.16 One of the shortcomings of the Nepal study was that the azathioprine was not used for a long enough duration.

Adverse effects due to azathioprine may occur in upto 15% of patients.21 The commonest adverse reactions that occur with azathioprine are nausea and vomiting and mucosal ulcers, occurring in 60% of patients.22 Azathioprine also causes significant bone marrow suppression (upto 5%) and can potentially cause leucopenia (3.8%), thrombocytopenia (2%) and even pancytopenia (0.4%).23 There may be an increased risk of infections and different malignancies. Pancreatitis, skin rashes and drug fever have been reported on rare occasions.24 Use of azathioprine in pregnancy has shown that the placenta may act as a barrier to its passage and current evidence of safety in pregnancy is reassuring.25, 26

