## Introduction:

## Study Aims

The primary aim of this study is to compare the neurological outcomes in patients with type 1 reactions and recurrent type I reactions in skin lesions, when they are treated with either Azathioprine in addition to a 20-week course of prednisolone or prednisolone alone.

The objectives of the study are: -

1. Improves dermatological outcomes in Type 1 reactions.

2. Improves neurological outcomes in Type 1 reactions and neuritis

3. Reduces the recurrence rate (i.e. requirement for further treatment with steroids) in patients with T1R and neuritis.

4. To compare the effectiveness of different duration of treatment with Azathioprine in T1R and neuritis.

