## Patient outcome measures

### Primary outcomes

1. **Recovery of nerve function**

- Absolute improvement in nerve function as measured by Voluntary Muscle testing (one point improvement in VMT score) and Sensory testing (two point improvement in ST score) using standard methods as defined in the field manual.

1. **Recurrence of neuritis during or after treatment**

- Recurrence of neuritis is defined as a new nerve function impairment presenting in the form of a decrease in VMT score by one point and an ST score by more than 2 points either during the study period or during the follow up period and present for two consecutive testings.

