### Secondary outcomes

1. Resolution of skin lesions
2. Recurrence of reaction manifest as skin reactions.

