## Statistical analysis

The primary analysis will be a comparison of azathioprine plus prednisolone with prednisolone alone for achieving the primary outcome following the “intention to treat” principle. Intention to treat analysis will also be performed for the secondary outcomes.

Analysis of endpoints, comparing time to event in the four arms will be performed.

Pre-planned sub group analysis will be performed for the following subgroups (male, female; MB, PB; previous T1R, new T1R).

A secondary on treatment analysis will be performed to explore the requirement of additional steroids as well as adverse effects with these drugs.

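### Objective 3 defines recurrence as needing further steroids, but no listed outcome measures that need, and its only named analysis is a secondary on-treatment one

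*Protocol*

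**What the plan says.** Four parts of the protocol bear on this.

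- **Study Aims, objective 3:** "Reduces the recurrence rate (i.e. requirement for further treatment with steroids) in patients with T1R and neuritis". Recurrence and further steroid treatment are presented as the same event.
- **Primary outcomes, item 2:** "Recurrence of neuritis is defined as a new nerve function impairment presenting in the form of a decrease in VMT score by one point", together with an ST fall of more than 2 points, present at two consecutive testings. Steroid use plays no part in this definition.
- **Secondary outcomes:** there are two items, resolution of skin lesions and "Recurrence of reaction manifest as skin reactions". Neither concerns steroids.
- **Statistical analysis:** the main comparison is "for achieving the primary outcome following the “intention to treat” principle", and "Intention to treat analysis will also be performed for the secondary outcomes". A further sentence reads "Analysis of endpoints, comparing time to event in the four arms will be performed". Additional steroids appear once: "A secondary on treatment analysis will be performed to explore the requirement of additional steroids".

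The Background reports that in the earlier Nepal trial the clinical outcomes were similar in the two groups, while "the overall dose of prednisolone was less in those on the combined regimen".

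**The concern.** An objective should lead to an outcome, and the outcome to an analysis that respects randomisation. For objective 3 that chain breaks twice. The event that the objective names is not on the outcome list. Its only named analysis uses a set that depends on what happened to patients after randomisation.

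This matters more than it would for a minor exploratory variable. The Background gives flare-up during tapering and prolonged steroid courses among its reasons for seeking an adjunct, and reports reduced steroid requirement as what the earlier trial found. If this trial gave a similar result, with clinical outcomes alike and less prednisolone used, the protocol would offer no intention-to-treat comparison to support the second half of that statement.

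**Working it through.** **1. Do the listed recurrence outcomes stand in for steroid need?**

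| Event | Where defined | Criterion |
| --- | --- | --- |
| Extra prednisolone | Patient Follow up: Management of Complications, item 1 | Worsening of neuritis or type 1 reaction leads to a step-up during the taper, or a restart after week 20 |
| Worsening of acute neuritis | Definitions | VMT down at least 1 point **or** ST down 2 points from baseline, in two consecutive testings |
| Recurrence of neuritis | Primary outcomes, item 2 | VMT down 1 point **and** ST down more than 2 points, at two consecutive testings |

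A patient who loses only ST points, or only VMT points, can have prednisolone stepped up without ever meeting primary outcome 2. Recurrence of skin reactions covers the skin route. Neither outcome captures the amount of prednisolone. The overlap is real but incomplete.

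**2. Does the time-to-event sentence help?** It covers endpoints, and steroid need is not a listed endpoint. The sentence names no analysis set.

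**3. What can an on-treatment comparison do?** The protocol does not define the set. For illustration, suppose it leaves out patients who stop blinded drug.

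Inputs:
- Rate of further steroids: 50%, from the Background. It comes from a 12-week course, so it is an assumption for this 20-week trial.
- Exclusion: 10%, borrowed from the adverse-reaction dropout in Sample size and applied first to an azathioprine arm only. The one-sided application is an assumption.
- q, the proportion of excluded patients who need further steroids: not in the protocol, so varied.
- No true effect.

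Rate shown on treatment = (0.50 − 0.10q) / 0.90, against 50% in an intact control arm:

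| q | Azathioprine rate | Apparent difference from 50% |
| --- | --- | --- |
| 0.3 | 0.47/0.90 = 52.2% | 2.2 points against azathioprine |
| 0.5 | 0.45/0.90 = 50.0% | none |
| 0.7 | 0.43/0.90 = 47.8% | 2.2 points in favour |
| 1.0 | 0.40/0.90 = 44.4% | 5.6 points in favour |

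If control also loses 5% with the same q, its rate is (0.50 − 0.05q)/0.95, which is 48.9% at q = 0.7 and 47.4% at q = 1.0. The apparent saving shrinks to 1.2 and 2.9 points. If both arms lose 10% with the same q, it is zero.

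**4. Is an intention-to-treat test worthwhile at the planned size?** The protocol's own figure reproduces: 2 × [(1.96 + 0.842) × 2 / 1]² = 62.8, hence 63 per group. Its inflated size is 78 per arm. For two proportions with arm sizes n₁ and n₂:

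power = Φ{[|p₁ − p₂| − 1.96 √(p̄(1 − p̄)(1/n₁ + 1/n₂))] / √(p₁(1 − p₁)/n₁ + p₂(1 − p₂)/n₂)}, where p̄ is the size-weighted mean rate.

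For 50% v 28.3% at 78 v 78: (0.217 − 1.96 × 0.0782)/0.0762 = 0.84, so power is about 80%. Solving for 80% power at two-sided 5%:

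| Control rate | Observed, control v azathioprine | Detectable azathioprine rate |
| --- | --- | --- |
| 50% | 78 v 78 | 28.3% |
| 50% | 78 v 234 (three arms pooled) | 32.2% |
| 50% | 58 v 58 (78 × 0.75 = 58.5) | 25.1% |
| 50% | 58 v 174 | 29.6% |
| 40% (assumed) | 78 v 78 | 19.6% |
| 40% (assumed) | 78 v 234 | 23.3% |

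Only large reductions are detectable with good power. The figures are illustrative, since the control rate is uncertain and the 78-per-arm rows assume nobody is lost.

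**The case against.** The strongest reply has four parts.

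*The clinical triggers are already tested as randomised.* Recurrence of neuritis and of skin reactions are intention-to-treat outcomes, and extra prednisolone follows worsening of either. This stands in part. A reader might infer that objective 3 cannot be answered at all from the listed outcomes. That goes too far: it is answered partly, and the gap is the or/and difference and the amount of drug.

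*A bias in favour of azathioprine is not shown.* A reader might infer that the on-treatment analysis will flatter azathioprine by 2 to 6 points. The protocol does not support this. That range needs 10% exclusion in azathioprine, none in control, and 70% to 100% of those excluded needing steroids. Sample size plans the same adverse-reaction dropout for every arm. More stopping in the azathioprine arms is plausible from the marrow toxicity in the Background, but is not stated. Nothing says that stoppers are treatment failures: the code-break criteria are laboratory ones, and patients who worsen receive more prednisolone and continue. This objection stands in full.

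*Analysis sets are commonly left to a statistical analysis plan.* That is fair for the definition of the on-treatment set. It does not answer the point, because the protocol itself chose that set for steroids and left steroids off its outcome list.

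*The steroid analysis is openly secondary and exploratory.* That is legitimate, and neurological outcome is the primary aim. But the other secondary outcomes receive intention to treat, and this one carries a numbered objective.

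**Conclusion.** The point holds as a mismatch between objective, outcome list and analysis set. Objective 3 names an event that no listed outcome measures, and the only analysis naming that event does not keep the randomised groups. This follows from the text and needs no numerical assumption.

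The direction and size of any bias are not established. Under the assumptions shown, the azathioprine rate could read anywhere from 52.2% to 44.4% when the truth is 50%, and the bias vanishes with equal exclusions and equal rates in both arms. The case for change is that the comparison is unprotected, not that it is known to favour one side.

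The point is of moderate weight. It leaves the primary comparison untouched, but it weakens the evidence on the effect that the Background reports from the earlier trial.

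**What to change.** 1. In Secondary outcomes, add need for prednisolone beyond the scheduled course (any step-up or restart), and total additional prednisolone.
2. In Statistical analysis, compare these by intention to treat in the allocated arms, and keep the on-treatment version, with its set defined, as a sensitivity analysis.
3. Reword objective 3 so that recurrence (as in primary outcome 2) and steroid requirement are two separately named outcomes.

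None of this alters a treatment rule. The costs go a little beyond a line of text:

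- One more secondary outcome is reported.
- The visit forms need checking. Patient follow-up procedure says that Forms 3.1 to 3.14 record end points, compliance and adverse effects. It does not mention prednisolone changes.
- Patients removed under the missed-visit and missed-treatment rules go back to routine care, so their later prednisolone use may not be collected. They should be analysed in their allocated arm up to the last observation, for example by time to first additional steroid, with the extent of missing data stated by arm.

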## Criteria for breaking the code

| Laboratory Parameter | Cut-off Point |
| --- | --- |
| Hb | < 7 g % |
| TLC | < 3000 |
| Platelet Count | < 1 lakhs |
| SGOT | > 50 |
| Creatinine | > 2 |

In case of abnormal blood counts, the following guidelines should be followed:

| Laboratory Parameter | Level | Action |
| --- | --- | --- |
| Total WBC | < 3 X 109/l | Break Code / Continue steroids |
| Absolute Neutrophil Count | < 1.0 X 109 /l | Break Code / Continue steroids |
| Absolute Neutrophil Count | < 0.5 X 109 /l | **If febrile**, start **antibiotic** and look for source of infection  As per guidelines in Field Manual |
| Hb | < 7.0 g/dl | Break Code / Continue steroids |
| Hb | Fall > 3 g/dl from baseline | **Break Code / Continue steroids** |
| Platelets | < 100000 | **Break Code/ Continue steroids** |
| Serum Creatinine | > 50 % above baseline | **Break Code / Continue steroids** |
| SGOT | > 2 X upper limit of normal | **Break Code / Continue steroids** |

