## Sample size

The sample size calculation was based on the expected improvements in the combined scores (skin, sensory & motor) that the addition of azathioprine to prednisolone would produce. It was calculated that the addition of azathioprine would produce a 25% improvement in the combined scores. This would be a score of 4 allowing for an alpha of 0.05 and beta of 0.80, the minimum sample size is calculated as follows:

n=2x[(Zα +Z1-β)xSD)/ d]2 =2x[(1.96+0.842))x2)/1]2 = 63 per group.

We assumed a ‘lost to follow up’ rate of 15%, and dropout rate due to adverse reactions of 10 %,so minimum of 78 patients would be required per arm, and a total of 312.

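### Added prednisolone, which objective 3 equates with recurrence, is not a listed outcome, and its only named analysis is an exploratory on-treatment one rather than intention to treat

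*Protocol*

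**What the plan says.** Study Aims, objective 3, reads: "Reduces the recurrence rate (i.e. requirement for further treatment with steroids) in patients with T1R and neuritis". Recurrence is thus expressed as a need for more steroids.

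The primary outcomes are recovery of nerve function and recurrence of neuritis. The secondary outcomes are resolution of skin lesions and "Recurrence of reaction manifest as skin reactions". Neither list contains an outcome for added prednisolone, whether as an event or as a dose.

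The Statistical analysis section applies intention to treat to the primary outcome and adds: "Intention to treat analysis will also be performed for the secondary outcomes". It also plans a time-to-event comparison of endpoints across the four arms. Additional steroids appear in one sentence only: "A secondary on treatment analysis will be performed to explore the requirement of additional steroids as well as adverse effects with these drugs". The protocol does not define the on-treatment set.

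Extra prednisolone is given under Management of Complications, item 1. If neuritis or the reaction worsens during the taper, the dose goes back up one step. If it worsens after week 20, prednisolone restarts at 40 mg. For abnormal counts, SGOT or creatinine, the Criteria for breaking the code give the action as "Break Code / Continue steroids".

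**The concern.** Steroid sparing is the effect for which the protocol has prior evidence. The Background describes an earlier azathioprine trial in leprosy with little difference in clinical results but less prednisolone on the combination, and it names the need for further steroids as a problem of current care. That effect would be judged in an analysis that conditions on what happens after randomisation.

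Who remains on treatment may depend on tolerance of azathioprine. A patient whose code is broken may stop study drug while prednisolone continues, so the outcome of interest still accrues after the event that could remove the patient from the set. A difference in added prednisolone could then be created or hidden by selection.

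**Working it through.** **1. Do the intention-to-treat outcomes already cover added prednisolone?**

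| | Motor condition | Link | Sensory condition |
|---|---|---|---|
| Recurrence of neuritis (Primary outcomes, item 2) | VMT down one point | and | ST down by more than 2 |
| Worsening of acute neuritis (Definitions) | VMT down at least one point | or | ST down two points |

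Both require two consecutive tests. The outcome is worded as "a decrease in VMT score by one point and an ST score by more than 2 points". The step-up rule refers to defined VMT and sensory criteria, and the worsening definition is the only one of that kind, so it is the apparent trigger. Read literally, three patterns can bring extra prednisolone without counting as a recurrence at that time: a motor-only fall, a sensory-only fall, and a motor fall with an ST fall of exactly 2. Skin flares are picked up by the second secondary outcome, but no listed outcome measures dose. Coverage is therefore partial.

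**2. How large could the bias be?**

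The protocol gives no figure for this, so what follows is an illustration.

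Inputs:
- Patients followed per arm: the Sample size section has 78 per arm and 15% lost, so 78 × 0.85 = 66.3, taken as 66. The three azathioprine arms together have 198.
- True need for added prednisolone: *p* = 50% in every arm, so there is no treatment effect. The 50% is the Background figure for a 12-week course. No 20-week figure is given.
- *e*: share of followed azathioprine patients excluded, with no controls excluded (assumed).
- *q*: share of those excluded who need added prednisolone (assumed).

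The on-treatment azathioprine rate is (*p* − *e*·*q*)/(1 − *e*), compared with 50% in controls.

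Example, *e* = 10%, *q* = 25%: (0.50 − 0.025)/0.90 = 52.8%, a false difference of 2.8 points. One arm then has 66 × 0.90 = 59.4 patients against 66. The standard error is about 0.0894 with pooled variance (null) and 0.0893 unpooled. The two tails are Φ[(0.0278 − 1.96 × 0.0894)/0.0893] ≈ 0.049 and Φ[(−0.0278 − 1.96 × 0.0894)/0.0893] ≈ 0.012, in total 6.1%.

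| *e* | *q* | Azathioprine rate | False difference | Actual error, one arm v control | Pooled v control |
|---|---|---|---|---|---|
| 5% | 25% / 75% | 51.3% / 48.7% | +1.3 / −1.3 | 5.3% | 5.4% |
| 10% | 25% / 75% | 52.8% / 47.2% | +2.8 / −2.8 | 6.1% | 6.7% |
| any | 50% | 50.0% | 0 | 5.0% | 5.0% |

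If exclusions and steroid need among the excluded are equal across arms, the false difference is zero. If 10% of azathioprine patients and 5% of controls are excluded, with *q* = 25% in both, the rates are 52.8% and (0.50 − 0.0125)/0.95 = 51.3%. The difference is 1.5 points and the error 5.3% (5.5% pooled).

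**3. Can selection also affect a real difference?**

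Assume 50% v 30%. Intention to treat has 65% power (83% pooled). On-treatment with *e* = 10% has 55% to 70% (75% to 88%) as *q* runs from 15% to 45%. Power can move either way.

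**The case against.** The strongest reply is that the protocol fixes little. It leaves the on-treatment set undefined, labels the analysis secondary and exploratory, and analyses both recurrence outcomes by intention to treat, with a time-to-event comparison across four arms. All of this stands, and much of objective 3 is tested as randomised. It does not remove the point, because the protocol itself names the method for additional steroids, and the listed recurrence outcomes are not the same measure.

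Four stronger readings are tempting and are not supported:

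- *That additional steroids will not be compared by randomised arm.* An on-treatment analysis can still be tabulated by arm. What is missing is a named analysis of the full as-randomised set.
- *That the Sample size section supplies a one-sided 10% exclusion.* Its "dropout rate due to adverse reactions of 10" per cent enters a target of 78 for every arm, control included. The one-sided 10% used in the working is an assumption.
- *That 15% of azathioprine patients would be excluded.* The Background says "Adverse effects due to azathioprine may occur in upto 15% of patients", which is any adverse effect and not stopping the drug. With *e* = 15% and *q* = 0 or 1, the formula gives 8.8 points and an error of 16.3% (23.3% pooled). That needs every extreme at once. The Background's bone marrow suppression figure is up to 5%.
- *That the code-break rule stops study drug.* It says only to break the code and continue steroids. Stopping study drug is a reasonable inference, but it is not stated, and the rule applies to placebo patients too.

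The mismatch between the recurrence and worsening definitions is a separate question of outcome definition. It is used here only to show that recurrence does not substitute for added prednisolone.

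**Conclusion.** The point holds at minor severity. The protocol gives the measure by which objective 3 defines recurrence no place among the outcomes and names only an on-treatment analysis for it. The intention-to-treat outcomes cover it in part.

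The bias is plausibly a few points and of unknown direction: zero with equal exclusions and equal steroid need, and about 1 to 3 points with 5% to 10% excluded from the azathioprine arms only and 25% or 75% of them needing steroids. These shares are assumed, as is the rule that stopping study drug means exclusion. The documents do not establish that exclusions differ by arm.

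A reader might go on to infer that extra prednisolone undermines the recovery analysis. It does not: that intention-to-treat comparison validly estimates the effect of a treatment policy that includes rescue, and nothing shows that rescue will be unequal.

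**What to change.** Add added prednisolone to the Secondary outcomes in two forms: time to first step-up or restart under Management of Complications, item 1, and total prednisolone dose to week 48. In Statistical analysis, make intention to treat across the randomised arms the main analysis of both. Keep patients whose code is broken or whose study drug stops in their randomised arm. Censor patients removed under the follow-up rules at their last visit, with a sensitivity analysis for informative removal. Keep the on-treatment analysis as supportive, state who is in it, and leave the recovery analysis as planned.

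The cost is a few lines in two sections and one or two analyses of data that the protocol already plans to use, with no change to care.

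The downside is incomplete steroid data. The Patient follow-up procedure removes patients who miss visits or four weeks of treatment, so their dose to week 48 goes unobserved. With 15% missing in each arm, an extreme bound turns an assumed 50% v 30% into 0.50 × 0.85 = 42.5% (no missing control needs steroids) v 0.30 × 0.85 + 0.15 = 40.5% (every missing azathioprine patient does). The sensitivity analysis is therefore needed. The on-treatment analysis has the same gap. The protocol already keeps assessing a patient who stops because of pregnancy, so follow-up after stopping is not foreign to it.
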